## Abstract

**Background:**

Shoulder arthroscopy frequently causes severe postoperative pain that may impede recovery. Liposomal bupivacaine provides prolonged analgesia, and ultrasound-guided superior trunk block (STB) offers comparable analgesia to interscalene block with a lower risk of hemidiaphragmatic paralysis. However, the optimal concentration of liposomal bupivacaine for STB remains unknown.

**Methods:**

This randomized, double-blind, controlled trial will enrol 282 adult patients scheduled for elective arthroscopic rotator cuff repair. Patients will be randomly allocated (1:1:1) to receive ultrasound-guided STB with liposomal bupivacaine 66 mg (Group A), 44 mg (Group B) or 33 mg (Group C), each diluted to 10 mL. The co-primary outcomes are (1) rest pain Numeric Rating Scale (NRS) score at 48 h post-surgery and (2) cumulative oral morphine milligram equivalents (MME) consumption within 0–48 h after surgery. Secondary outcomes include rest pain NRS scores at 6, 24 and 72 h; motor function assessed by Muscle Balance Scale, Bromage score and American Shoulder and Elbow Surgeons (ASES) score at 6, 24, 48 and 72 h; and Quality of Recovery-15 (QoR-15) score at 24 and 48 h.

**Discussion:**

This study will provide evidence on the optimal concentration of liposomal bupivacaine for STB in arthroscopic shoulder surgery, aiming to achieve effective and prolonged analgesia without compromising shoulder mobility.

## Introduction

The shoulder’s wide range of motion makes it vulnerable to injuries, often causing pain, stiffness and functional loss that can significantly impact daily life. These injuries are common across all ages, especially in middle-aged, elderly and physically active individuals. Standard treatments include open repair, minimally invasive surgery and shoulder arthroscopy. Guided by Enhanced Recovery After Surgery (ERAS) principles, clinicians prioritize early rehabilitation. Shoulder arthroscopy, being less invasive than open surgery, minimizes trauma and enables faster postoperative recovery, making shortened recovery time a key focus in managing shoulder injuries [1].

However, shoulder arthroscopy utilizes pressurized joint irrigation and controlled hypotension to optimize visualization and haemostasis, yet these measures contribute to tissue swelling and notable postoperative pain [2]. Prolonged pain compromises patient satisfaction and recovery, with the risk of acute pain transitioning to chronic states. Effective analgesia is therefore vital to facilitate rehabilitation, enhance quality of life and fulfil the objectives of ERAS protocols.

Ultrasound-guided interscalene brachial plexus block (ISB) enables precise nerve targeting, minimizes injury to surrounding structures and provides effective intraoperative analgesia, underscoring its value within ERAS protocols for shoulder surgery. Studies demonstrate that combining ISB with general anaesthesia improves perioperative outcomes compared to general anaesthesia alone [3–7]. However, a single ISB provides only transient analgesia [8], and while continuous nerve blocks can improve pain control [9], they are prone to failure and complications [10].

Liposomal bupivacaine, a long-acting local anaesthetic providing pain relief for up to 72 h [11], was recently FDA-approved for ISB [12,13] to offer prolonged analgesia. Evidence suggests it can extend analgesia duration and reduce opioid consumption after brachial plexus blocks [14–16]. Nonetheless, ISB carries a significant risk of hemidiaphragmatic paralysis (HDP). The superior trunk block (STB) has been proposed as an alternative, providing comparable analgesia while markedly lowering HDP incidence [17–20].

In practice, high-concentration liposomal bupivacaine for brachial plexus blocks may cause prolonged motor blockade and potential phrenic nerve involvement, which could hinder early rehabilitation [21]. Although STB has been shown to preserve phrenic nerve function while providing comparable analgesia to interscalene block [20], no study to date has systematically evaluated different concentrations of liposomal bupivacaine specifically for STB. The optimal concentration that balances effective, prolonged analgesia with preserved motor function remains unknown. To address this research gap, this study aims to identify the optimal concentration of liposomal bupivacaine for STB in arthroscopic shoulder surgery, seeking to achieve effective and long-lasting analgesia while preserving shoulder joint mobility.

## Patients and methods

This study will be conducted as a randomized, double-blind, controlled clinical trial. It was approved by the Ethics Committee of Shanghai General Hospital (Approval ID: 2024-209) on 27 November 2024 and the approved protocol was subsequently amended on 21 April 2026 (Approval ID: 2026-254). The protocol was registered with the Chinese Clinical Trial Registry (ChiCTR2400094688) on 26 December 2024 and the registry record was updated following the protocol amendment. We plan to recruit a total of 282 eligible patients from June 2026 to June 2027 (*n* = 94 per group) (Figure 1), all of whom will provide informed consent. The study will be conducted in compliance with the Declaration of Helsinki, and the protocol is reported per the Standard Protocol Items: Recommendations for Interventional Trials (SPIRIT) 2025 Statement: Updated Guideline for Protocols of Randomized Trials (Supplement 1)[22].

**Figure 1. F0001:**
[figure not shown]
Study flow diagram.

### Patients

The Inclusion criteria will be as follows: (1) adult patients aged ≥ 18 years old; (2) ASA classifications I-II; (3) scheduled to undergo elective arthroscopic rotator cuff repair; (4) demonstrate the ability to adhere to the study protocol and provide informed consent for participation in the clinical trial. Patients will be excluded if they meet any of these criteria: (1) history of upper limb neuropathy and chronic pain syndrome; (2) allergy to liposomal bupivacaine or other local anaesthetics (such as bupivacaine, ropivacaine or lidocaine); (3) severe respiratory disease; mental illness; cognitive impairment; drug or alcohol abuse; (4) long-term use of opioid (>3 months or Daily morphine intake >5 mg for 1 month); (5) contraindications to general anaesthesia or interscalene brachial plexus block; (6) pregnancy status.

### Randomization and blinding

An independent research coordinator, who will not be involved in the subsequent study, conducted the online randomization using a 1:1:1 allocation ratio and a permuted block size of 3. Subjects will be allocated to either Group A (liposomal bupivacaine 66 mg), Group B (liposomal bupivacaine 44 mg) or Group C (liposomal bupivacaine 33 mg) based on a random sequence (Figure 1). The doses were selected based on the following rationale. Notably, these dose selections remain partly exploratory, as robust pharmacodynamic and dose-response data for liposomal bupivacaine specifically in the superior trunk block (STB) are currently lacking. Nonetheless, the FDA-approved dose for interscalene block (ISB) is 133 mg. ISB targets the C5-C7 nerve roots at the interscalene groove. In contrast, STB is performed more caudally and laterally at the convergence of the C5 and C6 nerve roots, where they form the superior trunk of the brachial plexus. At this location, STB maintains comparable analgesia while allowing for lower local anaesthetic doses. Accordingly, we selected 66 mg (50% of the ISB dose) as the high-concentration group for STB. Second, 33 mg (25% of the ISB dose) was chosen to explore the minimal effective concentration. Third, 44 mg, the midpoint between 33 mg and 66 mg, was selected to identify the optimal balance between analgesia and motor function preservation. This trial is therefore designed to define the optimal concentration for STB. Allocation concealment will be ensured through the use of identical opaque sealed envelopes. An independent anaesthesia nurse at each study centre will be responsible for preparing the study medications. Given that varying concentrations of liposomal bupivacaine exhibit distinct appearances, we will maintain blinding for the surgeons and operating room staff by transferring the medication into identical opaque syringes, labelled solely with the patient’s identification number. The STB procedures will be conducted by a qualified anaesthesiologist, who will not participate in anaesthesia management or the supervision of postoperative care. All additional perioperative clinical care will adhere to the standard practices of the institution. Pertinent data will be documented in the trial case report form (CRF).

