### Sample size estimation

Sample size calculation was performed using PASS 2021 software (NCSS, USA) based on a previous study [24,25] and our preliminary data, with the goal of ensuring adequate power for both co-primary endpoints.

For the 48-hour moderate-to-severe pain incidence (dichotomized NRS): Based on our preliminary dose-finding results, the incidence of moderate-to-severe pain at 48 h was assumed to be 15% for Group A (66 mg), 25% for Group B (44 mg) and 35% for Group C (33 mg). Without optimized long-acting regional analgesia, approximately 74.3% of patients experience moderate-to-severe pain following arthroscopic rotator cuff repair [24,25]. Assuming 1-β = 0.8, α = 0.05 and *R* = 1, 84 participants per group are required.

For the co-primary outcome of cumulative 0–48 h opioid consumption (MME, continuous): Based on our preliminary data and published literature, the mean cumulative MME within 0–48 h was assumed to be 20 mg (SD = 12) in Group A, 35 mg (SD = 12) in Group B and 50 mg (SD = 12) in Group C. Using one-way ANOVA for three-group comparison with α = 0.05 and power = 0.8, 72 participants per group are required.

The larger requirement (84 per group) was adopted to provide ≥80% power for each co-primary endpoint. To allow for a 10% dropout rate, we will enrol 94 patients per group, resulting in a total sample size of 282 participants.

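### One published block size of 3 for three arms lets anyone who learns two allocations in a block deduce the third; the risk depends on unmasking and is cheap to reduce

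*Protocol article*

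**What the plan says.** All the relevant statements but two are in the section Randomization and blinding of the protocol article.

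- **Sequence.** A coordinator with no later part in the study "conducted the online randomization using a 1:1:1 allocation ratio and a permuted block size of 3". One size is given. Varying sizes and stratification are not mentioned.
- **Concealment.** "Allocation concealment will be ensured through the use of identical opaque sealed envelopes".
- **Drug preparation.** "An independent anaesthesia nurse at each study centre will be responsible for preparing the study medications". This nurse therefore knows each dose.
- **Masking.** The reason given for opaque syringes is this: "Given that varying concentrations of liposomal bupivacaine exhibit distinct appearances". The syringes carry only the patient's identification number. The people they are said to blind are the surgeons and operating room staff. The anaesthesiologist who performs the block takes no part in anaesthesia management or postoperative care, but is not named as blinded.
- **Assessment.** Under Data collection, postoperative follow-up is restricted to investigators who do not know the group.
- **Size.** Under Sample size estimation: "we will enrol 94 patients per group, resulting in a total sample size of 282 participants".

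Under Patients and methods, recruitment is planned from June 2026 to June 2027, so the block size is public before the planned start.

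**The concern.** When the block size equals the number of arms, each block is one of the six orderings of A, B and C. Two known allocations settle the third, and one known allocation narrows the other two. A sealed envelope hides its content from view, but does not stop that content being worked out from earlier patients.

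Allocation concealment exists to prevent selective enrolment or timing by someone who knows the next arm. Blinded outcome assessment does not protect against that. Small blocks also make masking more fragile, because one accidental unmasking carries information about its neighbours in the block. The co-primary outcomes here are a patient-reported pain score and opioid use under analgesic care tailored to the patient. Knowledge of the dose could influence both.

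**Working it through.** **Inputs from the protocol article.** Three arms, 1:1:1, fixed block of 3 (Randomization and blinding); 84 per group before dropout, 10% dropout, 282 in total (Sample size estimation).

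**Assumptions, not in the article.** How many earlier allocations a guesser knows; whether centres share one list; how many centres there are.

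**1. The plan's own total.** 84 / (1 − 0.10) = 93.3, rounded up to 94; 94 × 3 = 282. This matches. 282 / 3 = 94 complete blocks.

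**2. Block of 3, all earlier allocations known.** The chance of a correct best guess is 1/3 in position 1, 1/2 in position 2 and 1 in position 3.

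- Certain allocations: 94 / 282 = 33.3%.
- Average best guess: (1/3 + 1/2 + 1) / 3 = 61.1%, against 33.3% with no blocking.

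**3. One list shared by c equal centres in random order.** A site knows its own allocations and their list positions, nothing else. Let p = 1/c be the chance that a given earlier patient in the block was at the same site.

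- Certain share = p² / 3.
- Best guess, position 2 = p/2 + (1 − p)/3.
- Best guess, position 3 = p² + 2p(1 − p)/2 + (1 − p)²/3.

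Two centres (p = 1/2):
- certain = 1/12 = 8.3%;
- best guess = (1/3 + 5/12 + 7/12) / 3 = 44.4%.

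Three centres (p = 1/3):
- certain = 1/27 = 3.7%;
- best guess = (1/3 + 7/18 + 13/27) / 3 = 40.1%.

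**4. Alternatives, all earlier allocations known.** The fixed blocks are exact enumerations. The random mix was simulated over sequences of 282, with the three sizes equally likely. Its guesser knows the set of sizes but not which size is in use, and updates on the sequence so far.

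| Scheme | Certain | Best guess correct |
|---|---|---|
| Fixed 3 (as planned) | 33.3% | 61.1% |
| Fixed 6 | 20.0% | 56.1% |
| Fixed 9 | 14.3% | 53.2% |
| Random 3, 6, 9 | about 4% | about 55% |
| No blocking | 0% | 33.3% |

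If the guesser is also told where each block starts, the random mix gives about 7% certain and 55% correct.

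The average guess improves only modestly, from 61% to about 55%. The main gain is that certain allocations fall from one in three to about one in 25.

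**5. Imbalance from the random mix.** If enrolment stops inside a block of 9, each arm has between 0 and 3 patients in that block. Two arms can therefore differ by at most 3, against 94 planned per arm.

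**The case against.** The strongest reply is that this is a masked trial, and that the harm needs one person who both knows earlier allocations and can influence enrolment or care. The article names nobody in both roles. The coordinator leaves after generating the list, the preparing nurse is independent and has no stated recruitment or assessment task, and the block operator is kept out of later care. Syringes are opaque and coded, and follow-up is blinded. All arms receive the same drug in the same 10 mL volume. The assumed rates of moderate-to-severe pain at 48 h (15%, 25% and 35%) overlap so much that a patient's course says little about the dose. A preparer who knows the doses is also a feature of many masked trials, whatever the block size.

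Most of this stands, and it rules out the stronger reading that a reader might infer: that concealment has failed for a third of the trial, or that 94 allocations will be known in advance. The article shows no route by which earlier allocations reach those who enrol, and does not say whether centres share a list. The figure of 94 is an upper limit for a guesser with complete knowledge of the past.

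The reply does not remove the point. The safeguards limit leakage, while the block size determines how much a leak reveals, and here that is the maximum possible. The nurse sees every dose, the article does not exclude contact between the nurse and those who enrol, and the block operator is not listed among the blinded.

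**Conclusion.** The point holds as a conditional weakness in a stated design choice. The method is valid, and the article contains no contradiction or arithmetic error on it. A single, published block size equal to the number of arms makes any two known allocations in a block reveal the third.

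The size depends on what becomes known:

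- **Full knowledge of earlier allocations:** up to 33.3% certain and 61% guessed correctly.
- **One shared list, a site knowing only its own patients and their list positions:** 8.3% and 44% with two equal centres, 3.7% and 40% with three. The number of centres and the sharing are assumptions.
- **Masking intact and no leakage:** no allocation can be deduced in this way.

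This is a potential risk to concealment and masking, not demonstrated bias. It is worth acting on because the remedy is cheap and has to come before allocation starts.

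**What to change.** If recruitment has not begun, rerun the randomisation program with randomly varying block sizes, such as 3, 6 and 9. The wording suggests that a list may already exist, in which case it should be replaced before the first patient is randomised. Withhold the sizes from site staff until enrolment ends, then report them. In the protocol, replace the stated size with a sentence saying that sizes vary at random and are held by the independent coordinator.

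A separate list for each centre is optional and not needed for this fix. It places whole blocks within a site, so on predictability alone it gives no advantage over a shared list.

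The cost is one rerun, a wording change and a possible final imbalance of a few patients (at most 3 between any two arms with a single list).

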### Anaesthesia management

Prior to the induction of general anaesthesia, all participants will receive an ultrasound-guided STB. General anaesthesia will be induced using i.v. sufentanil 0.25 μg/kg, propofol 2 mg/kg and rocuronium 0.6 mg/kg. Anaesthesia will be maintained with desflurane at a concentration of 0.8–1.2 MAC, in conjunction with remifentanil administered at a rate of 0.2–0.3 µg/kg/min. Hemodynamic events, including hypotension (>30% decrease in mean blood pressure from baseline), hypertension (>30% increase in mean blood pressure from baseline), bradycardia (heart rate <50 beats/min) and tachycardia (heart rate >50 beats/min), fluid administration and other anaesthetic interventions will be managed by attending anaesthesiologists. A standardized Enhanced Recovery After Surgery (ERAS) protocol will be applied.

Rescue analgesia with intravenous flurbiprofen axetil (50 mg) will be administered as needed for pain with an Numeric Rating Scale (NRS) score ≥4. All analgesic management will be tailored to the patient’s perioperative condition and documented by the clinician.

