### Study interventions

A single ultrasound-guided STB will be administered in the pre-anaesthesia room 1 hour preoperatively. The STB procedure will be performed by a qualified anaesthesiologist under sterile conditions. The patient will be placed in the supine position with the head turned slightly to the contralateral side. A high-frequency linear ultrasound transducer (6–13 MHz) will be positioned in the supraclavicular fossa with a transverse oblique orientation. The brachial plexus will be identified, and the superior trunk (formed by the C5 and C6 nerve roots) will be visualized as a hypoechoic structure lateral to the subclavian artery. A 22-gauge, 50-mm echogenic needle will be inserted using an in-plane approach from lateral to medial, with the needle tip placed adjacent to the superior trunk. Following negative aspiration, the assigned dose of liposomal bupivacaine (66, 44 or 33 mg) will be diluted with normal saline to a total volume of 10 mL and injected in 2–3 mL aliquots under real-time ultrasound guidance to ensure proper spread. Block success will be confirmed 15 min after injection by assessing sensory loss (cold test) and motor weakness (reduced strength of deltoid and biceps muscles) compared with the contralateral side. Following the block procedure, patients will undergo continuous electrocardiogram (ECG) monitoring for 1 hour to enable immediate management of any serious adverse events. Known side effects of STB include nausea, vomiting, constipation, tachycardia, bradycardia, dizziness, headache, somnolence and hypoesthesia. The most serious risk is arrhythmia due to inadvertent intravascular injection, which ultrasound guidance helps to mitigate. Mild adverse events will not require treatment; moderate-to-severe events will receive appropriate pharmacologic intervention. If a severe event occurs after 50% of the dose has been administered, the injection will be discontinued immediately. Acute allergic reactions will be managed according to standard institutional protocols. All adverse events will be fully documented in the case report form.

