### Primary and secondary outcomes

The co-primary outcomes will be (1) Rest pain NRS score at 48 h post‑surgery; (2) Cumulative opioid consumption within 0–48 h after surgery, converted to oral morphine milligram equivalents (MME). Secondary outcomes will be (1) Rest pain NRS scores at 6 h, 24 h and 72 h post‑surgery; (2) Muscle Balance Scale (MBS) ratings at 6 h, 24 h, 48 h and 72 h; (3) Motor nerve block assessed by the Bromage score at 6 h, 24 h, 48 h and 72 h [23]; (4) American Shoulder and Elbow Surgeons (ASES) functional score at the same intervals (Table 1); (5) Quality of Recovery-15 (QoR-15) score at 24 h and 48 h post‑surgery.

**Table 1. t0001:** The American shoulder and elbow surgeons (ASES) score.

Activity	Unable to do Score = 0	Very difficult to do Score = 1	Somewhat difficult Score = 2	Not difficult Score = 3
Do usual work				
Do usual sport				
Put on a coat				
Sleep on your painful or affected side				
Wash back/do up bra in back				
Manage toileting				
Comb hair				
Reach a high shelf				
Lift 4.5kg above shoulder				
Throw a ball overhand				
Total scores				

A patient-reported subjective rating system was employed to assess the score, comprising two components: pain (50%) and functional capacity (50%), with a total possible score of 100. Higher scores indicate superior shoulder function.

Specific scoring method: pain score = (10-NRS score) *5; Functional score = total score of 10 items *5/3.

ASES score = pain score + function score.

Although liposomal bupivacaine provides analgesia lasting up to 72 h, its most stable and clinically consistent effect occurs within the first 48 h after surgery. This period also represents the critical window for early postoperative rehabilitation, opioid consumption and acute pain control. Therefore, 48 h was selected as the primary time point to capture the most clinically meaningful analgesic difference among groups, while 72 h was retained as a secondary outcome to assess the extended duration of action.

NRS scores range from 0 (no pain) to 10 (worst imaginable pain). Mild pain (1–3) is non‑disruptive to sleep, moderate pain (4–6) mildly disrupts sleep and severe pain (7–9) prevents or awakens from sleep.

The MBS assesses elbow and wrist flexion strength using a 5‑point scale: 0 (no muscle activity), 1 (slight movement), 2 (movement against gravity only), 3 (movement against resistance with reduced strength) and 4 (strong movement against resistance).

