### Data collection

Table 3 outlines the schedule of enrolment, interventions and data measurements in accordance with the SPIRIT guidelines. Demographic data, ASA status, comorbidities, preoperative medications and the age-adjusted Charlson Comorbidity Index (aCCI) are scheduled to be collected prior to anaesthesia. Surgical, anaesthesia and perioperative data, including hemodynamic events, will be documented *via* an electronic system.

**Table 3. t0003:** Schedule of patient enrolment, study interventions, and outcome assessment according to SPIRIT statement.

			Study period				
Timepoint	Enrollment Preoperative visit	Allocation Before surgery	Post-allocation				
			Pre-anesthesia room	6 h	24 h	48 h	72 h
Enrollment							
Inclusion criteria	×						
Exclusion criteria	×						
Written informed consent	×						
Baseline data	×						
Randomization		×					
Allocation		×					
Study interventions							
Group A			**×**				
Group B			**×**				
Group C			**×**				
Outcome assesment							
NRS score				**×**	**×**	**×**	**×**
MME						**×**	
MBS score				**×**	**×**	**×**	**×**
Bromage score				**×**	**×**	**×**	**×**
ASES score				**×**	**×**	**×**	**×**
QoR-15 score					**×**	**×**	

To minimize reporting errors in the study, only investigators who will be blinded to the study design and group assignment will conduct the postoperative follow-up, which will include assessments of postoperative pain and motor block. Outcome measures will be documented and evaluated in accordance with the procedures outlined in the blinded section. An independent Data Monitoring Committee (DMC), composed of an attending orthopaedic surgeon, an attending anaesthesiologist, a pharmacist and a statistician, will oversee the conduct of the study.

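### Bradycardia and tachycardia share one cut-point of 50 beats/min, so as written the recorded tachycardia count would say almost nothing about dose

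*Protocol article*

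**What the plan says.** The protocol article lists four kinds of hemodynamic event under Anaesthesia management. The heart-rate pair is "bradycardia (heart rate <50 beats/min) and tachycardia (heart rate >50 beats/min" (closing bracket omitted). The blood-pressure pair is relative to the patient's own baseline: "hypotension (>30% decrease in mean blood pressure from baseline", with hypertension as the mirror image. The sentence goes on to place these events, along with "fluid administration and other anaesthetic interventions will be managed by attending anaesthesiologists".

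Two other sections bear on how the events are captured.

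- Data collection: "Surgical, anaesthesia and perioperative data, including hemodynamic events, will be documented" in an electronic system.
- Study interventions: "Known side effects of STB include nausea, vomiting, constipation, tachycardia, bradycardia", among others. No threshold is given there. The same section adds: "All adverse events will be fully documented in the case report form".

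Anaesthesia management is the only place in the article that gives tachycardia a numerical definition.

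**The concern.** A definition of an abnormal event has to leave some values that are not abnormal. This pair leaves only one, a rate of exactly 50. The text defines events that clinicians are to manage and that the trial is to document, so a field or automatic flag built from it would mark ordinary heart rates as events.

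What is at stake is the usefulness of one part of the safety record. In a trial of three doses of a local anaesthetic, a reader would expect tachycardia counts to be summarised by arm, if only descriptively. If nearly everyone has the event, such a table cannot separate the doses. The same holds for any count of patients with at least one hemodynamic event, if tachycardia is a component.

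**Working it through.** The plan gives no figure here to reproduce: no sample size, power or error rate rests on these definitions. Three checks apply.

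**1. Coverage of the definitions.** Bradycardia is the set of rates below 50 and tachycardia the set above 50. Of the whole-number rates from 30 to 180 beats/min, only 50 falls in neither. For mean blood pressure, by contrast, everything from 30% below to 30% above baseline is outside both definitions. The sentence therefore allows a normal band for pressure and none for heart rate.

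**2. How many patients would be labelled tachycardic.** This depends on a heart-rate distribution that the documents do not give. Assume that one reading per patient is normal with mean *m* and standard deviation *s*. Then P(rate > 50) = 1 − Φ((50 − *m*)/*s*). For *k* independent readings, the chance of at least one above 50 is 1 − (1 − p)^*k*.

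| Assumed mean, SD (beats/min) | One reading > 50 | At least one of two > 50 |
|---|---|---|
| 55, 12 | 66.2% | 88.5% |
| 60, 10 | 84.1% | 97.5% |
| 65, 10 | 93.3% | 99.6% |
| 70, 10 | 97.7% | 99.95% |
| 75, 8 | 99.9% | about 100% |

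The first row, for example, has (50 − 55)/12 = −0.417, so p = 0.662 and 1 − (1 − 0.662)² is about 0.885. The first and last rows are the extremes of the grid examined (mean 55 to 75, SD 8 to 12). Readings within a patient are correlated, so the two-reading column is somewhat high for two adjacent readings. Monitoring throughout an operation gives many more than two, which pushes the share up again.

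**3. What a near-ceiling rate does to a contrast between two arms.** Take 94 per group, two-sided α = 0.05, and the usual normal approximation: power = Φ((|p₁ − p₂| − 1.96·SE₀)/SE₁), with SE₀ from the pooled and SE₁ from the separate proportions.

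- 99% against 99.5%: SE₀ and SE₁ are both about 0.0126, so (0.005 − 1.96 × 0.0126)/0.0126 is about −1.56 and power is about 6%.
- 10% against 25%: SE₀ = 0.0554 and SE₁ = 0.0543, so (0.15 − 0.1086)/0.0543 is about 0.76 and power is about 78%.

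All four rates are hypothetical, and the approximation is rough near 100%. The two contrasts also differ in size, and that is the point: when almost every patient has the event, there is no room for a difference of useful size.

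**The case against.** The strongest reply is that nothing the trial has promised to analyse is harmed, and most of that reply stands. A reader might infer that a planned comparison of hemodynamic event rates between doses is void. The article sets out no such comparison. The outcomes section begins with "The co-primary outcomes will be (1) Rest pain NRS score at 48 h post‑surgery" and goes on to opioid consumption, pain, motor, function and recovery scores. Hemodynamic events are not among them and have no row in the assessment schedule (Table 3). They are not named under Sample size estimation or Statistical analysis, where there is only a general rule for categorical variables. The Discussion describes the trial as mainly pharmacodynamic and leaves the safety profile to larger studies.

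A reader might also infer that a dose-related arrhythmia signal would be lost. The documents do not support that either. The arrhythmia risk under Study interventions concerns injection into a vessel. It is watched by an hour of continuous ECG after the block, and neither the ECG monitoring nor the adverse event recording refers to the 50 beats/min cut-point.

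Third, saturation is not certain. The figure looks like a typographical slip that staff may not follow, and the case report form and electronic system are not shown. That limits the consequence but does not remove the error. If staff substitute limits of their own, the definition behind the recorded counts is undocumented and may differ between anaesthesiologists, or between centres, since the article refers to more than one. If they follow the text, the count is saturated. Neither gives a tachycardia count that can be defended.

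**Conclusion.** The definition is wrong as written, and nothing elsewhere in the article corrects it. Its reach is narrow: the recorded tachycardia count, any composite hemodynamic event rate that contains it, and the labelling of ordinary heart rates as events to be managed. The bradycardia, hypotension and hypertension definitions can be used as they stand. The co-primary and secondary outcomes and the sample size are untouched.

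That both definitions together cover every rate but 50 follows from the text alone. That practically every patient would be labelled tachycardic rests on two conditions: that the text is applied literally, and that heart rate is read repeatedly. On a single reading, the assumed distributions give 66% to 99.9%. The severity is minor.

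**What to change.** Before the first patient is enrolled, the sponsor should reconcile the two heart-rate definitions under Anaesthesia management. The intended values are for the clinical team to supply, and none is proposed here. The sponsor should also check that neither the case report form nor the electronic record carries the shared cut-point, and that both use the reconciled definition. The cost is a one-line correction to the protocol and a check of the data-capture forms. The article gives recruitment as starting in June 2026; a correction made before then avoids recoding collected data.
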